#### Secondary outcomes

Physical function: It primarily includes sarcopenia (muscle mass, muscle strength, and physical function), the Fried Scale, and International Physical Activity Questionnaire Short Form (IPAQ-SF).Sleep: Pittsburgh Sleep Quality Index (PSQI).Nutritional status: the multi-nutritional assessment short form (MNA-SF) and body mass index (BMI).Mood disorders: Patient Health Questionnaire-9 (PHQ-9) Scale, and the Generalized Anxiety Disorder-7 (GAD-7) Scale.The plasticity of multidimensional intervention on cognitive impairment biomarkers: The influence of the multidimensional intervention on cognitive impairment biomarkers was studied by micro-protein post-translational modification, metalomics, metabolomics, transcriptomics, and other technologies and compared with AD molecular markers to determine their relationship with disease severity and outcome. To explore the effects of the multidimensional intervention on brain perfusion, iron content, β-amyloid protein, Tau protein and phosphorylated Tau protein, deacetylase 1, IL-6, IGF-1, nitric oxide, platelet, ubiquitin, C-reactive protein, hemocysteine, and other key indicators, quantitative susceptibility mapping (QSM), structural MRI imaging, fluid attenuated inversion recovery (FLAIR) sequence, amyloid and tau PET were used.

### Data collection and analysis

#### Data collection methods

Cognitive-related professional assessments (Table 4) will be performed on all formally enrolled participants during enrollment and exit, including basic personal information collection, comprehensive assessment of cognitive health, physical condition assessment, functional MRI testing, biological samples testing/ storing, and wearable device monitoring (sports watches).

**Table 4 Tab4:** Contents list of participants’ enrollment and exit evaluation

Data Type	Dimension	Details/tools
Basic personal information collection	General units	Name, gender, age, ID number, place of birth, length of local residence, local residential address, telephone number (her/himself + relatives), educational background, nationality, language (minority language), and main occupation before 60 years old.
Comprehensive assessment of cognitive health	Cognitive function	MoCA Scale, MMSE Scale, DSST Scale, AVLT-H Scale, STT Scale, AFT Scale, and BNT-30 Scale
	Daily living ability	ADL Scale, and IADL Scale.
	Mental	PHQ-9 Scale, and GAD-7 Scale.
	Sleep	PSQI Scale.
	Nutrition	MNA-SF Scale.
	Physical exercise	IPAQ-SF Scale.
	Sarcopenia	SARC-F Scale.
	Frail	FRAIL Scale.
	Social function information	SSRS Scale.
	Others	Previous disease history, hospitalization history \ Medication status \ diet, drinking, and smoking.
Physical condition assessment	General units	Body mass index, blood pressure, waist-hip ratio, biceps circumference, triceps skinfold thickness, arm span, and calf circumference.
	Sarcopenia	Handgrip strength (Xiangshan EH102), six-meter walk, five-time chair stand test, appendicular skeletal muscle mass and BIA (Inbody 770).
Functional magnetic resonance imaging testing	Cognitive related units	T1, T2, T2flair, DWI, BOLD, DTI.
Biological samples testing/ storing	Informed sample testing information	Blood routine, biochemistry, trace elements, inflammatory factors, hormones, stool, and urine routine.
	Cryopreserved samples (-80 ˚C)	Blood and stool.
Wearable device monitoring (Huawei band6 sports watches)	Sleep data	Total sleep duration, deep sleep duration, and light sleep duration.
	Movement data	Heart rate.

Note: MoCA, Montreal Cognitive Assessment; MMSE, Mini-mental State Examination; DSST, Digit Symbol Substitution Test; AVLT-H, Auditory verb learn test-Huashan; STT, Shape Trails Test; AFT, Animal Fluency Test; BNT, Boston Naming Test; ADL, Activities of Daily Living; IADL, Instrumental Activities of Daily Living; PHQ-9, Patient Health Questionnaire-9; GAD-7, Generalized Anxiety Disorder-7; PSQI, Pittsburgh Sleep Quality Index; MNA-SF, Multi-Nutritional Assessment Short Form; BIA, Bioelectrical Impedance Analysis; IPAQ-SF, International Physical Activity Questionnaire Short Form; SARC-F, Sarcopenia-Five; SSRS, Social Support Rating Scale; DWI, Diffusion Weighted Imaging; BOLD, Blood Oxygenation Level Dependent; DTI, Diffusion Tensor Imaging

#### Statistical methods

To compare the results of cognitive assessment among groups, quantitative data analysis will use IBM SPSS version 21.0 [27] and Python version 3.0 [28] software, relying on the analysis of variance, covariance, and other methods. Mean, standard deviation (SD), median, and range will describe continuous variables. Counting, proportion, the Wilcoxon test, and other methods will be used to analyze categorical variables. Classify and compare the normal distribution, homogeneity of variance and other data features of each variable in all the data, preliminarily screen variables with statistical differences, and combine professional knowledge to use these variables as alternative variables for subsequent comparative analysis and model training. Graphical summaries such as boxplots, case profiles, and labeled dispersion maps will be used to compare the distribution of intervention variables in each group and participant characteristics between groups. A linear mixed model will be used to simulate longitudinal changes in primary responses between groups, allowing for missing data (assuming data is missing at random) and within-subject correlations for repeated measures over time, with the model adjusting for baseline response variables and other covariates as needed. The effectiveness analysis (Full Analysis Set, Per Protocol Set) will be performed to assess the overall effect of the intervention.

Using data analysis techniques such as regression, chi-square, T-test, rank-sum test, normality test, decision tree, support vector machines, XGBoost, CATBoost and artificial intelligence deep learning, this study will rely on multi-modal data, take training effect and cognitive improvement as label values, and build a prediction and intervention model of mild cognitive dysfunction supported by artificial intelligence technology. Simultaneously, our team will apply explicable machine learning theory to explain the variables in the model and try to create new ideas for the basic research direction.

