### Sample size and groups

In the present study, the sample size is determined primarily by the following factors: [1] It is difficult to maintain the compliance of the community population, which necessitates a significant investment of workforce by the research team to maintain compliance; [2] The quality control difficulty of multidomain intervention is high, and more human and material resources required in supervising the quality of each link of the research; [3] Screening of potential subjects in the community requires high time and cost; [4] Due to the reasons of research content and funding, the number of our team members is limited; [5] MCI prevalence was set as P = 0.34 [25], power = 0.95, and dropout rate = 0.2. Therefore, considering scientific and practical feasibility and other factors, according to the sample size calculation method of RCT study [26], the total sample size of the single center would be 90, with 30 participants in each community. We have given the basis for calculating the sample size of a single sub-center. However, because China has a large geographical area, each region may have different characteristics. Therefore, in the study design, we calculated the sample size required by only one sub-center, in order to balance the influence of different regional bias factors on the overall effect of the study by adding sub-centers in different regions into the overall study, so as to evaluate the effect of multi-domain intervention more objectively. Therefore, this study intends to include 12 sub-centers to participate, with a total sample size of 1080.

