#### Primary outcomes

Cognitive function: The assessment methods included the Montreal Cognitive Assessment (MoCA) Scale, the Subjective Cognitive Decline (SCD-Q9) Scale, the Auditory verb learn test-Huashan version (AVLT-H) Scale, the Shape Trails Test (STT-A/B) Scale, the Animal Fluency Test (AFT) Scale, the Boston Naming Test (BNT) Scale, and the Self-Consciousness Scale (SCS).Magnetic Resonance Imaging (MRI): T1, T2, T2flair, Diffusion Weighted Imaging (DWI), Blood Oxygenation Level Dependent (BOLD), and Diffusion Tensor Imaging (DTI).

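### The comparative analysis takes candidate variables from a significance screen of the trial data, so the efficacy covariates are chosen after the fact and exit measurements are not excluded

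*Protocol article*

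**What the plan says.** The rule stands in the first paragraph of Statistical methods, which deals with comparing cognitive results among the groups. The features to be examined are those of "data features of each variable in all the data". From these the team will "preliminarily screen variables with statistical differences, and combine professional knowledge to use these variables as alternative variables for subsequent comparative analysis and model training". No threshold is given. The text does not say which groups or which visit the differences refer to.

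The same paragraph then gives the efficacy model: "A linear mixed model will be used to simulate longitudinal changes in primary responses between groups", "with the model adjusting for baseline response variables and other covariates as needed". The baseline value of the response is therefore fixed, and every other covariate is open.

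The machine-learning prediction model is described separately, in the next paragraph. Data collection methods states that the Table 4 assessments are made at both enrolment and exit.

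**The concern.** The sentence names two uses, comparison and model training, and it sits in the paragraph on group comparison. It cannot be read as feature selection for the prediction model alone. For the efficacy comparison it raises three problems.

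- **Wrong criterion.** If the differences are between groups, a covariate enters because it happened to be unbalanced. Whether it predicts cognition plays no part.
- **Late choice.** A data-driven candidate list, filtered by judgement and combined with covariates added as needed, means that the adjustment set is decided with the results in reach.
- **No time limit.** Nothing confines the screen to baseline. Exit sleep, nutrition and activity scores are in Table 4, and the multidomain programme is meant to change them. Adjusting for them would remove part of the effect that the trial sets out to measure.

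**Working it through.** The document states no alpha or error rate for the screen, so there is no figure of its own to reproduce. The steps below size the consequences.

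**Inputs from the document.** Sample size and groups gives "the total sample size of the single center would be 90, with 30 participants in each community", so a two-group comparison has 30 + 30 = 60 people in one centre. It also gives "this study intends to include 12 sub-centers to participate, with a total sample size of 1080", so over 12 centres a two-group comparison has 12 × 60 = 720, or 360 per arm.

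**Assumptions.** Screening and test level 0.05 two-sided; 30 candidate baseline covariates, 10 of them prognostic (coefficient 0.15 each); individual randomisation; no clustering; no drop-out.

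**1. What an imbalance screen keeps.** Under randomisation each baseline covariate differs between two groups at p < 0.05 with probability 0.05, whatever its prognostic value. Of the 10 prognostic covariates it keeps on average 10 × 0.05 = 0.5. Of the 20 irrelevant ones it keeps 20 × 0.05 = 1.0. Any given strong predictor is left out 95% of the time.

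**2. Type I error of the treatment test after covariate screening.** 20,000 null trials per sample size, Monte Carlo standard error about 0.0015.

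| Model | n = 60 | n = 720 |
|---|---|---|
| No added covariates (stands for a set fixed in advance) | 0.049 | 0.047 |
| Covariates kept for a between-group difference | 0.044 | 0.044 |
| Covariates kept for association with the outcome | 0.050 | 0.048 |
| Most favourable of the three | 0.081 | 0.071 |

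The first row is an exact test with true level 0.05, so its 0.047 shows the simulation noise. Screening followed by one model does not inflate the error, and selection on imbalance is slightly conservative. Inflation comes from being free to choose among the models.

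**3. Adjusting for an exit variable that the intervention has moved.** In a linear model with standardised variables:

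adjusted effect = total effect − (within-arm slope of outcome on exit variable) × (shift of exit variable between arms)

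The document gives neither quantity, so both are assumed.

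- Shift 0.3 SD, slope 0.3: 0.3 × 0.3 = 0.09 SD is taken off the effect.
- Low end, shift 0.2 and slope 0.1: 0.02 SD.
- High end, shift 0.4 and slope 0.5: 0.20 SD.

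Such a variable is likely to pass the screen. With 360 per arm the standard error of a standardised difference is √(2/360) = 0.0745. A shift of 0.3 gives z = 0.3/0.0745 = 4.02, and the chance of p < 0.05 is P(Z > 1.96 − 4.02) = 0.98. For a shift of 0.2, z = 2.68 and the chance is 0.77. Clustering would lower these chances but would not change the bias.

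**The case against.** The strongest defence has four parts.

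- **The screen is not mechanical.** It yields candidates, to be combined with professional knowledge, and the same sentence serves model training, where feature screening is usual. This stands for the prediction model. It does not help the efficacy comparison, which the sentence also names, because judgement applied after seeing which variables differ is still a late choice.
- **The most important covariate is already fixed.** The baseline response enters whatever the screen shows. This stands, and it limits the precision lost when other predictors are left out.
- **A covariate list is commonly left to the analysis plan.** This stands for the open-ended covariate phrase taken alone. It does not cover the screen, which is a stated method.
- **The error rate holds.** This also stands: one model fitted after covariate screening stays at or just below 0.05. A reader might infer that every later p-value is invalid. That does not follow. The inflation in step 2 needs a choice among models after the results are seen, which the document permits but does not prescribe.

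A reader might also infer that outcomes are screened, so that only those already significant are compared. The reference to all the data does not rule this out, but the document does not state it. Primary outcomes lists the cognitive tests ("Cognitive function: The assessment methods included the Montreal Cognitive Assessment (MoCA) Scale, the Subjective Cognitive Decline (SCD-Q9) Scale", and others) and the MRI sequences ("T1, T2, T2flair, Diffusion Weighted Imaging (DWI), Blood Oxygenation Level Dependent (BOLD), and Diffusion Tensor Imaging (DTI"). Secondary outcomes lists the rest, and the mixed model is applied to the primary responses. Nothing drops or promotes an outcome according to the screen. How several primary outcomes share the error rate is a separate question.

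**Conclusion.** The point holds for the choice of covariates in the efficacy comparison. The plan prescribes a significance screen on the trial data, does not confine it to the prediction model, does not restrict it to baseline, and leaves the further covariates open.

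The harm to the type I error is conditional: none if one screened model is used (0.044 to 0.050), and about 0.07 to 0.08 if the most favourable of three may be reported. These figures rest on the simulation assumptions above, including no clustering.

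The more serious risk is to the estimate. If an exit variable that the intervention has changed becomes a covariate, the treatment effect is biased, by 0.02 to 0.20 SD over the assumed range and by 0.09 SD at its middle. The document does not say that exit variables will be used in this way; it fails to exclude them. The wording should be changed before outcome data by group are examined.

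**What to change.** In Statistical methods:

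1. Remove the screening step from the comparative analysis.
2. Name the efficacy covariates in advance and use the same set for every outcome: baseline value of the outcome, age, sex, education and sub-centre. Replace the open-ended covariate phrase with this list.
3. State that no variable measured after randomisation enters the efficacy model as a covariate.
4. Keep data-driven variable selection for the exploratory prediction models, carried out inside cross-validation that holds out whole communities.

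The cost is wording only. Age, sex, education and the baseline scores are already collected under Table 4, and sub-centre is known from the design. No visit, measurement or participant is added.

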**Methods:**

Our study was designed as a national multicenter, community-based randomized controlled trial (RCT). Twelve medical institutions in ten Chinese cities will participate in our study from 2020 to 2024, and 1080 community residents aged 50 and above will be enrolled as participants. Each sub-center will be responsible for 90 participants (30 people per community) across three communities (non-contact control group, health education group, and multidomain intervention group). The community will be the basic unit of the present study, and all participants in each community will receive the same intervention/control measure. Three working groups are set up in each sub-center to manage the three communities independently to minimize interference at the implementation level between the groups. The multidomain intervention group will receive integrated interventions including exercise, nutrition, sleep, health education and mindfulness meditation. All data generated by the research will be analyzed and processed by statistical software (such as SPSS 21.0, Python 3.0, etc.), and part of the research data will be displayed in the form of graphs and tables.

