### Assignment of interventions

#### Sequence generation

The randomization of the code is shared by the data platform manager and PI. Whole random process of this study mainly consists of two steps. The first step is to carry out the random assignment work with the community as the basic unit, select 3 communities at random within the main urban area of the city where the sub-center is located, and use the computer generator randomizer method to determine the intervention content of each community. The second step of the random process is to carry out random assignment with individual residents as the basic unit, and the computer generator randomizer method is used to randomly screen all the candidate subjects in each community who have completed all assessments and are willing to participate in this study, finally the final list of subjects in each community is randomly confirmed. The PI will collect the participants’ cell phone number list and community list, and the data platform manager will use the computer generator randomizer method to match each cell phone number with a random code. The PI then distributes the community and participant codes to the community managers, who use them to carry out the sequence generation.

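### Arms are assigned to whole communities, but the stated group comparison leaves out the correlation within a community, so its standard errors are too small

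*Protocol article*

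**What the plan says.** All places are in the protocol article.

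- **Unit of the study.** The Methods part of the abstract states: "The community will be the basic unit of the present study, and all participants in each community will receive the same intervention/control measure". Trial design and study setting repeats that everyone from one community gets the same intervention.
- **Unit of randomisation.** Under Sequence generation, the first step is to "carry out the random assignment work with the community as the basic unit" and to "use the computer generator randomizer method to determine the intervention content of each community". The second step draws residents at random within each community: "finally the final list of subjects in each community is randomly confirmed". That step selects participants and does not allocate them to arms.
- **Numbers.** Under Sample size and groups, "the total sample size of the single center would be 90, with 30 participants in each community", and "this study intends to include 12 sub-centers to participate, with a total sample size of 1080". A dropout rate of 0.2 is assumed there.
- **Measurement times.** Under Data collection methods, the cognitive assessments "will be performed on all formally enrolled participants during enrollment and exit".
- **Analysis.** Statistical methods compares cognitive results among groups by analysis of variance, covariance and other unnamed methods, lists the Wilcoxon test for categorical variables, and adds a linear mixed model for longitudinal change. That model allows for "within-subject correlations for repeated measures over time, with the model adjusting for baseline response variables and other covariates as needed". The article mentions no community effect, ICC, design effect, cluster-robust variance or community-level analysis.

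**The concern.** The randomisation supplies 36 independent units, while the named analyses work on individual participants. The one correlation that is named joins two measurements on the same person. It does not join the roughly 30 people who share a community.

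Those people are unlikely to be independent. They share a neighbourhood and a community manager. In the active arms they are also taught as a group. Under Adherence strategy, participants are told to talk with one another after group sessions so that peers reinforce the effect, and attendance rankings are posted weekly in a shared online group.

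If that correlation is left out, chance differences between communities are read as differences between arms. Confidence intervals for the main comparison are then too narrow and p-values too small, and a positive result could not be taken at face value.

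**Working it through.** **Inputs from the protocol article**
- Sub-centres 12, communities per sub-centre 3, participants per community 30, dropout 0.2.

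**Assumptions, because the article gives no figure**
- Two-sided 5% test.
- ICC of 0.01, 0.02 or 0.05, the same in all arms, meaning the correlation left after any baseline adjustment.

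**1. The plan's own total.** 12 × 3 × 30 = 1080, as stated. This gives 36 communities, 12 per arm. After dropout, m = 30 × 0.8 = 24 per community, or 12 × 24 = 288 per arm.

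**2. Design effect and type I error for two arms.** DE = 1 + (m − 1) × ICC. The correct standard error is √DE times the one that ignores community. The type I error is 2 × (1 − Φ(1.96/√DE)). The effective number per arm is 288/DE.

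| ICC | DE (m = 24) | √DE | Type I error | Effective n per arm |
|---|---|---|---|---|
| 0.01 | 1 + 23 × 0.01 = 1.23 | 1.11 | 7.7% | 234 |
| 0.02 | 1 + 23 × 0.02 = 1.46 | 1.21 | 10.5% | 197 |
| 0.05 | 1 + 23 × 0.05 = 2.15 | 1.47 | 18.1% | 134 |

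With all 30 retained, the type I error is 8.4%, 11.9% and 21.1%.

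**3. Simulation of the layout (three arms, 12 communities per arm, m = 24)**

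| Analysis | ICC 0 | 0.01 | 0.02 | 0.05 |
|---|---|---|---|---|
| Two-arm comparison of individuals | 4.8% | 8.0% | 10.1% | 18.0% |
| Three-arm ANOVA of individuals | 4.8% | 8.7% | 12.6% | 24.7% |
| Same ANOVA with sub-centre added | 4.8% | 8.8% | 12.7% | 25.2% |
| Community-level analysis blocked by sub-centre | 4.9% | 5.0% | 5.1% | 4.9% |

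The first row agrees with the formula. The three-arm test has its own, larger inflation because two contrasts are tested together.

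**4. Does the within-subject term help?** In a separate simulation of 2000 runs per setting, a mixed model with enrolment and exit values as responses and a subject effect only (equivalent to an analysis of change) rejected in 8.9%, 12.3% and 26.2% of runs at ICC 0.01, 0.02 and 0.05. Baseline-adjusted ANCOVA rejected in 8.6%, 12.3% and 25.7%. The community effect acted on the exit outcome in both. Neither form restores the error rate.

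**5. Why sub-centre does not help.** Each sub-centre has one community per arm. A sub-centre term removes what the three communities share. What is particular to one community remains mixed with its arm.

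**6. Degrees of freedom for the correct analysis.** 36 communities − 1 (mean) − 11 (sub-centres) − 2 (arms) = 22.

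**The case against.** The strongest defence is that this is a condensed article, that no statistical analysis plan is shown, and that random-effects structure is commonly settled there. The text does not say that within-subject correlation is the only one allowed, and its other methods and its covariates as needed leave room. What stands is that the harm follows only if the omission is carried into the analysis. What does not stand is that the point is merely unstated detail. The article does describe the correlation in its main model, and it names a level other than the one it randomises. A later plan written faithfully to this text would inherit the mismatch.

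Some stronger readings are tempting but not supported:

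- **T-tests between arms.** A reader might infer that t-tests, chi-square and rank-sum tests are also planned for comparing arms. Statistical methods lists them in the paragraph on building the prediction model. The point rests on ANOVA, ANCOVA and the mixed model.
- **An idle within-subject term.** With two assessments and baseline as a covariate, a reader might infer that the within-subject term has nothing to model. If enrolment and exit values are both responses, it does real work, and the article does not settle which is meant. The inflation is the same either way.
- **The missing sub-centre block as a cause.** Leaving out the block is a matter of precision and of matching the design. The simulation shows that it does not drive the error rate.
- **A known error rate.** No significance level or ICC is stated, so no single figure is the trial's true error rate. A common ICC is a further simplification, because the non-contact arm has no group sessions.

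**Conclusion.** The point holds and should be corrected before the outcome data are analysed. The stated group comparison does not match the unit of randomisation, and its standard errors are too small for any positive ICC.

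The direction needs no further assumption. The size does: over the assumed ICC range, standard errors should be 1.11 to 1.47 times larger, and a nominal 5% comparison of two arms would reject a true null hypothesis in about 7.7% to 18.1% of trials. At an ICC of exactly zero there would be no inflation, but group delivery and deliberate peer contact make that hard to rely on. The conclusion concerns the analysis as the article words it. It does not show that an unseen analysis plan repeats the omission.

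**What to change.** Replace the mixed-model sentence in Statistical methods, and carry the same text into the analysis plan:

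> Each cognitive outcome at exit is analysed with a linear mixed model with fixed effects for arm, sub-centre (the randomisation block) and the baseline value of that outcome, and a random intercept for community. Kenward-Roger or Satterthwaite degrees of freedom are used (about 22 with 36 communities). A community-level analysis blocked by sub-centre is the sensitivity analysis. Individual-level ANOVA, ANCOVA and Wilcoxon comparisons between arms are descriptive only.

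Sub-centre is included for consistency with the design and for precision. The community term is what corrects the error rate. If enrolment and exit values are both kept as responses, the model also needs a community effect on the change over time, because a community intercept that is constant over time cancels out of the change.

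**Cost.** A change of wording. Community and sub-centre define enrolment and allocation, so no new data are needed. The downside is wider confidence intervals, by the factors above and slightly more for the 22 degrees of freedom.

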#### Randomization, allocation and concealment

The roles involved in the implementation of the study in each sub-center included PI, data platform manager, participant, community manager (research team), community partner, multidimensional intervention implementation team, health education implementation team, cognitive assessment team, and radiology testing team. A computer generator randomizer method (PI execution) is used to determine the intervention content in each community, and PI is responsible for conducting specific research work in each sub-center. This study could not achieve a perfect “blinding” because the participants are able to clearly perceive the intervention, but we tried to maximize the “isolation” of the intervention/control implementation team in each group to reduce the interaction between the groups.

The intervention/control settings of the three communities in each sub-center are assigned by the platform manager using the computer generator randomizer method to achieve the randomization process in our study.

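### The arms are randomised in sub-center blocks of three communities, but the stated mixed model fixes neither the block nor the community; both terms are needed, and they should be added together.

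*Protocol article*

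**What the plan says.** **Design.** The abstract makes the community the unit: "The community will be the basic unit of the present study". Under Sequence generation, the first random step is to "select 3 communities at random within the main urban area of the city where the sub-center is located". Under Randomization, allocation and concealment, "The intervention/control settings of the three communities in each sub-center are assigned by the platform manager using the computer generator randomizer method". Trial design and study setting gives each sub-center one control, one health education and one multidomain community. Under Sample size and groups, "the total sample size of the single center would be 90, with 30 participants in each community", and "this study intends to include 12 sub-centers to participate, with a total sample size of 1080".

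**Reason for 12 sub-centers.** The same section expects regions to differ and adds centers "in order to balance the influence of different regional bias factors on the overall effect of the study by adding sub-centers in different regions".

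**Analysis.** Statistical methods lists analysis of variance, covariance and other methods. It then describes a linear mixed model that allows for within-subject correlation over time, "with the model adjusting for baseline response variables and other covariates as needed". It names no sub-center term and no community term, and it rules out neither.

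**The concern.** The design has two levels above the participant. Community is what was randomised, so differences between communities belong in the error of the arm contrast. Sub-center is the block, so differences between sub-centers cancel from the arm contrast and do not belong in its error. The written model fixes its correlation structure and baseline adjustment but leaves out both design terms, and the block would enter only if judged necessary.

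The two omissions act in opposite directions. Leaving out community makes standard errors too small and tests too liberal. Leaving out sub-center makes the error term too large, but this shows to any extent only when community is in the model. A sponsor who corrects the first omission alone would therefore meet the second, and could miss a real effect because regional variance sits in the standard error.

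**Working it through.** **Inputs from the protocol article.** 12 sub-centers × 3 communities = 36 communities; 3 × 30 = 90 per sub-center; 12 × 90 = 1080, so the stated totals check. The planned dropout ("MCI prevalence was set as P = 0.34 [25], power = 0.95, and dropout rate = 0.2") leaves 30 × 0.8 = 24 evaluable per community. The 30 per community cannot be reproduced, because alpha and effect size are not given; nothing below depends on that derivation.

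**Assumptions.** The protocol gives no ICC, SD or effect size. Total variance is set to 1, with sub-center share c of 0.02, 0.05 or 0.10, community share k of 0.02 or 0.05, and residual e = 1 − c − k. Tests are two-sided at 5%.

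**Variance of the difference between two arms (12 communities each, 24 per community).**

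- True variance: 2(k + e/24)/12. The sub-center share c is absent because each sub-center has one community in each arm.
- Reported by the model as written: 2/(12 × 24) = 0.00694, SE 0.0833.
- Reported with sub-center only: 2(1 − c)/(12 × 24).
- Reported with community only: 2(c + k + e/24)/12.
- Reported with both terms: equals the true variance.

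**Worked case, c = k = 0.05.** Here e = 0.90 and k + e/24 = 0.05 + 0.0375 = 0.0875.

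- True SE: √(2 × 0.0875/12) = 0.1208.
- As written: 0.0833/0.1208 = 0.690, so the nominal limit 1.96 acts as 1.96 × 0.690 = 1.352, and the true error rate is 17.6%.
- Sub-center only: √(2 × 0.95/288) = 0.0812, true error rate 18.7%. This is slightly worse than as written.
- Community only: √(2 × 0.1375/12) = 0.1514, which is 1.25 times the true SE.

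**Degrees of freedom.** 36 communities − 3 arms = 33 without the block; 33 − 11 = 22 with it.

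**Without a community term** (normal approximation; the rejection rate is for an assumed true difference of 0.30 SD):

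| k | c | True error, as written | True error, sub-center only | Rejection rate, as written → sub-center only |
|---|---|---|---|---|
| 0.02 | 0.02 | 10.2% | 10.6% | 91.4% → 91.7% |
| 0.02 | 0.05 | 9.9% | 10.8% | 91.6% → 92.3% |
| 0.02 | 0.10 | 9.3% | 11.1% | 92.0% → 93.2% |
| 0.05 | 0.02 | 17.9% | 18.4% | 86.9% → 87.2% |
| 0.05 | 0.05 | 17.6% | 18.7% | 87.1% → 87.8% |
| 0.05 | 0.10 | 17.1% | 19.4% | 87.4% → 88.8% |

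**With a community term** (simulated community means, 60,000 runs per setting; in each row the effect gives 80% power when both terms are present, about 0.29 SD for k = 0.02 and 0.35 to 0.36 SD for k = 0.05):

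| k | c | Power, both terms (22 df) | Power, community only (33 df) | True error, community only |
|---|---|---|---|---|
| 0.02 | 0.02 | 80% | 72% | 2.6% |
| 0.02 | 0.05 | 80% | 57% | 1.1% |
| 0.02 | 0.10 | 80% | 36% | 0.4% |
| 0.05 | 0.02 | 80% | 75% | 3.2% |
| 0.05 | 0.05 | 80% | 65% | 1.7% |
| 0.05 | 0.10 | 80% | 49% | 0.6% |

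At c = 0.01 the loss is about 2 to 3 points. At c = 0 the model without the block has about 81% power, so the block costs about 1 point.

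**The case against.** **The large power losses do not describe the written plan.** This stands. A reader might infer from the blocked design that the present plan loses substantial power and gives intervals that are too wide. The first table shows otherwise. With community unmodelled the intervals are too narrow, the block alone changes the rejection rate by no more than about 1.4 points, and adding it alone slightly raises an inflated error rate.

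**The balance is already in the estimate.** This also stands. With one community of equal size per arm in each sub-center, sub-center effects cancel from the arm difference whether or not the model has a block term (approximately so under unequal dropout). It would be wrong to say that regional differences bias the comparison or that the aim of adding sub-centers is defeated. Only the standard error is affected.

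**Baseline adjustment is ignored in the calculation.** This stands in part. The mixed model adjusts for the baseline response, which removes some of the stable regional and assessor differences. What remains is mainly sub-center variation in six-month change. It need not be negligible: the cognitive assessment team is listed among each sub-center's roles and is drawn mainly from temporary student recruits, although they receive common training.

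**The term is unnamed, not excluded.** This is correct. The covariate list is open, and an analysis plan that is not shown may name both terms, so the documents do not support saying that every planned analysis omits sub-center. But the article does write out the model's correlation structure and adjustment. The terms that follow from the randomisation should be fixed there, not left to need.

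**The communities are not matched.** This is correct. They are drawn at random within the city, so the design is blocked by sub-center and not matched on community characteristics.

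**Conclusion.** The point holds as a mismatch between the randomisation and the stated model. Community and sub-center both follow from the design, and neither is fixed in the analysis. As written, the serious consequence is a true error rate of about 10% or 18% at an assumed community ICC of 0.02 or 0.05; the block's own contribution there is at most 1 to 2 points of power. If clustering is repaired by a community term alone, the loss from the missing block runs from 5 points (80% to 75%) to 44 points (80% to 36%) over the assumed ICCs. Those losses are at the upper end, because the calculation has no baseline covariate and every ICC is an assumption. The direction and the remedy do not depend on the exact values.

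**What to change.** In Statistical methods, state that every between-arm model of a primary outcome includes sub-center (12 levels) as a block effect, a community-level term and the baseline score, with the arm contrast tested on about 22 denominator degrees of freedom. The levels should be the 12 sub-centers and not the 10 cities, since three sub-centers share Chengdu and communities are allocated within sub-center. The sub-center term should not be added without the community term, because that leaves the tests too liberal.

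The change needs one sentence and no new data. It uses 11 degrees of freedom (33 to 22), about 1 point of power if sub-centers do not differ. It is best made before outcome data are seen.
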